### Intervention: family-centered approach

Before data collection started, all CHPs, that is, nurses and medical doctors (N = 57), from the intervention region attended group training sessions lasting four days in total before working using the family-centered approach. Training sessions consisted of background information on the family-centered approach, work instructions, role-play sessions, and discussing practical cases. After the group training sessions, the CHPs practiced the family-centered approach during routine well-child visits. Within one month after the training sessions, CHPs were asked to videotape two well-child visits which they discussed with, and which were evaluated by, trainers using standardized guidelines [20]. This procedure was repeated until the trainer and CHP rated the performance of the CHP as adequate. After passing this assessment, intervision groups of CHPs with trainers were held every three months in order to monitor performance.

The family-centered approach covers five domains associated with psychosocial development which are discussed from the perspective of parents. Domains discussed are: Competence of the parent, Role of the partner, Social support, Perceived barriers or life events within the care-giving context, and Wellbeing of the child. For each domain, several questions regarding that specific domain are asked, intertwined in a conversation, by the CHP (see Additional File 1: Appendix 1). During the second well-child visit at age 8 weeks, the nurse is allotted 15 minutes extra (added to the routine 15 minutes, i.e., 30 minutes in total) to discuss the 5 domains exhaustively. During every routine well-child visit, any possible parental concerns will first be elicited which will provide a starting point for further communication. For all the questions in the family-centered approach, CHPs will be able to register important information as not discussed, a protective factor, not known, or a risk factor. Furthermore, for each domain, the results of the conversation will be able to be summarized as not discussed, a protective factor, not known, or a risk factor, and subsequently an explanation will be able to be provided. Based on the information about the different domains, the parent and the CHP will jointly decide whether there are any concerns. If there are any, an additional activity (for example, an appointment to further clarify these or an intervention) will be planned. In communication with the parents, building a relationship of trust and empowerment of the parents are central features of the family-centered approach. Parents are regarded as experts on their child and in their own strengths, which may function as protective factors that can be enhanced to stimulate positive psychosocial development of the child.

### Control condition: care as usual

The care as usual provided by CHPs (N = 49) involves examining and monitoring the general health and psychosocial development of children during regular well-child visits of 15 minutes. During the well-child visit, CHPs follow the Guidelines of the Dutch National Centre for Preventive Child Healthcare [24]. This center provides, monitors, and improves on the national guidelines regarding monitoring developments in Dutch PCH (http://www.ncj.nl).

### Outcome measurements

There will be several primary outcomes from this study. The first of these will be the proportion of psychosocial problems identified by the CHPs in both the intervention and control regions. When the child is aged 2 to 14 months, the focus will be on social-emotional development, for children of 18 months of age behavioral problems will be taken into account as well. A second primary outcome will be the predictive value of CHPs' identifying psychosocial problems when a child is between 2 and 14 months old, and later at 18 months, in both the intervention and control conditions. The last primary outcome will be the concordance between the risk and protective factors as assessed by CHPs using the family-centered approach domains (Competence of the primary caretaker, Role of the partner, Social support, Perceived barriers or life events within the care giving context of the child, and Wellbeing of the child) and the outcomes on standardized questionnaires filled in by the parents in the subsample regarding these domains.

The secondary outcomes in the study will be the degree to which the needs of the parents are met and their willingness to disclose their concerns.

### Measurements

Social-emotional and behavioral development will be assessed by both the CHPs and the parents. CHPs will indicate during each routine well-child visit between the ages of 2 and 18 months whether psychosocial development is fine, not optimal (but no extra care is needed), or whether there is a problem, indicating that an additional activity is needed. The definition of an additional activity is used to assess whether risks for or actual psychosocial problems exist. From 2-14 months, parents in the subsample of the study will assess the social-emotional development of their children by filling in the Ages and Stages Questionnaire Social Emotional (ASQ-SE) [25,26], an internationally validated questionnaire containing 22 to 29 items for children aged 3 to 60 months. When the child is 18 months of age, all participating parents will fill in the Child Behavioral Checklist (CBCL) 1.5-5, an internationally validated instrument containing 100 items that assesses psychosocial problems [22,23].

The competence of the primary caretaker will be assessed by CHPs within the family-centered approach format by registering whether the competence is regarded as a protective factor, unknown, or a risk factor. Parents from the subsample will indicate their competence by answering 11 items in the Dutch Parental Stress Index (PSI) [27]. Furthermore, the Setting Self-efficacy subscale (14 items) of the Problem Setting and Behavior Checklist (PSBC), measuring the confidence of the primary caretaker in mastering problem situations [28], and the Parental Sense of Competence scale (PSOC), 16 items measuring the competence of the parent [29] will be used. With the SF-12, an abbreviated version of the 36-Item Short Form Health Survey [30,31], the health status (physical and mental) of the parent will be assessed.

The role of the partner will be assessed by CHPs by indicating whether the role can be seen as a protective, unknown, or risk factor. Parents in the subsample of the study will assess the relationship between the partners using the 12-item General Functioning (GF) subscale of the McMaster Family Assessment Device (FAD) that addresses the emotional relationships within families [32,33]. Furthermore, having a baby and the effect on the relationship between the partners will be assessed using the subscale "relationship" of the Dutch Parental Stress Index (5 items) [27].

Social support will be assessed by the CHPs by registering whether this can be perceived as a protective factor, unknown, or a risk factor. In the additional interview of the subsample, parents will indicate their social support by making use of a short version of the Social Support List (SSL, short version) [34], containing 12 items addressing the social support experienced. Furthermore, the Loneliness score, containing 11 items assessing feelings of overall, emotional, and social loneliness [35], will be used.

Perceived barriers or life events within the care-giving context of the child will be assessed by the CHPs by indicating in the family-centered approach format whether these can be seen as a protective factor, unknown, or a risk factor. Parents in the subsample will indicate the barriers they perceive within the care-giving context of the child by using a questionnaire measuring the relationship between basic requirements and potential deprivations for the child (e.g., nutrition) and the financial situation of parents [36]. Furthermore, a list with 17 items of life events which happened in the past year, derived from the Dutch Parental Stress Index [27], will be used.

The met and unmet needs of parents will be assessed using a family-centered questionnaire designed for this study, filled in by all participating parents when the child is 2 and 18 months of age, which assesses the needs and experiences of parents in terms of PCH.

Willingness to disclose will be measured by asking all parents to rate the following statement: "I feel free to discuss all kinds of worries with the PCH professionals" on a Likert scale from 1 (= not true at all) to 5 (= very true) when the child is 2 and 18 months of age.

Other outcome measurements will deal with the background characteristics assessed at baseline, including children's and parents' ages and genders, parental educational level, employment status, country of birth, and length of time living in the Netherlands. In the subsample, possible biological vulnerabilities within the family will also be assessed by asking participants whether there are any family members familiar with different kinds of psychopathology.

### Sample size and power calculation

In a study regarding children aged 2-4 years, PCH identified psychosocial problems in 10-12% of all children, of these 22-23% were confirmed by clinical scores on the CBCL filled in by parents [37]. For the current study, an increase in the predictive value of 20% for the family-centered approach is considered to be relevant, resulting in an identification rate of 42%. With a power of 80% and a .05 alpha, 85 "cases" in both regions of the country will be needed to detect a change in predictive value of 20%.

Based on birth statistics in both the intervention and control regions, approximately 2,500 births are expected [38] within one year in both the intervention and control regions. With an expected participation rate of 70%, this would result in 1,750 participating families in both conditions within the inclusion period of one year. With an expected cumulative incidence of 10% of children with social-emotional problems between 2 and 14 months, this would result in 175 "cases" in both conditions. We anticipate that 70% of "cases" will agree to participate, so that 121 "cases" and 242 matching control families can be invited for complementary interviews. For this group, we anticipate that for 70% of included "cases" a complete dataset will be collected.

### Time frame

The aim is to have an inclusion period of one year. As it is uncertain whether an identification rate of psychosocial problems of 10% will be feasible when the child is between 2 and 14 months of age, the inclusion period can be spread over a period of 20 months. Consecutively, CHPs will then ask parents who visit the PCH center with their newborns to participate before the child reaches the age of 3 months. When the child reaches the age of 2-14 months, "cases" and matching control families will be enrolled in the subsample. The final measurement for all participating families will take place when the child is 18 months of age, and will be spread over a period equal to the length of inclusion.

### Statistical analyses

To compare the baseline characteristics of the participants in the intervention and control regions, chi-squared tests for categorical variables and t-tests for continuous variables will be used. If the intervention and control regions differ regarding the background characteristics of the children, appropriate multivariable analyses will be done using standard and logistic regression analyses to adjust for these differences.

Regarding the primary outcomes of the study, the following analysis will be performed. First, we will compare the proportion of, and risks for psychosocial problems identified by the CHPs in both the intervention and control conditions when the child is between 2 and 14 months of age and when the child is 18 months of age, using chi-squared tests and logistic regression analysis to correct for potential differences between regions. Second, we will assess the sensitivity, specificity, and the positive and negative predictive values of social-emotional and psychosocial problems identified by CHPs in both conditions, using the ASQ-SE [25,26] for children aged 2-14 months from the subsample and using the CBCL [22,23] for all participating children when the child is 18 months of age. Third, we will compare kappas as a measurement of agreement between the protective and risk factors assessed by the CHPs, and relevant reference questionnaires as filled in by the parents from the subgroup.

For the secondary outcomes of the study, we will compare met and unmet needs of the parents between conditions using independent t-tests and multivariate regression analysis to correct for potential differences in background characteristics. The level of willingness to disclose concerns will be compared using ordinal regression analysis.

Data will be analyzed using SPSS 18.0. The significance level is set at .05.

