## Methods/design

### Design

In a quasi-experimental design, those regions in which the family-centered approach has already been implemented (intervention condition) will be compared to those regions where care as usual has been maintained (control condition). Overall, the regions in the family-centered care condition and the control condition are comparable for socio-demographic variables, including income, working participation, ethnicity, and percentage of single-parent households. In Figure 1 the design of the study is described schematically. Randomization per child/family is not possible in this setting as professionals provide care to all children in the region in which they work, in other words, contamination is inescapable in case of individual randomization. We will minimize the likelihood of contamination by prohibiting overlap between CHPs working in both the intervention and control conditions, and by informing CHPs about the activities to be undertaken for data collection in both conditions, separately. We chose a quasi-experimental design because full cluster-randomization was not possible due to implementation of the family-centered approach in a number of regions before the study started. To exclude those factors outside the intervention would affect the outcomes; no innovations regarding the psychosocial development of children aged 0-18 will be implemented in either the intervention or the control regions.

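### Confounder adjustment in this non-randomised comparison hangs on baseline tests of the children's characteristics, and none is named for the predictive values that set the sample size

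*Protocol article*

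**What the plan says.** The Design section describes a comparison of existing regions without randomisation: "In a quasi-experimental design, those regions in which the family-centered approach has already been implemented (intervention condition) will be compared". It adds that, overall, "the regions in the family-centered care condition and the control condition are comparable for socio-demographic variables", naming income, working participation, ethnicity and single-parent households.

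The Statistical analyses section opens with a comparison of participants' baseline characteristics, for which "chi-squared tests for categorical variables and t-tests for continuous variables will be used". The general rule on adjustment follows: "If the intervention and control regions differ regarding the background characteristics of the children, appropriate multivariable analyses will be done". The section closes with "The significance level is set at .05".

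The wording then varies by outcome:

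- **Share of children identified (first primary outcome):** chi-squared tests, plus logistic regression to correct for regional differences.
- **Sensitivity, specificity and predictive values (second primary outcome):** to be assessed in both conditions; no adjustment named.
- **Kappas (third primary outcome):** to be compared; no adjustment named.
- **Parents' needs (secondary):** t-tests, plus regression to correct for background differences.
- **Disclosure (secondary):** "The level of willingness to disclose concerns will be compared using ordinal regression analysis".

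The background variables listed under Measurements are the ages and genders of children and parents, and "parental educational level, employment status, country of birth, and length of time living in the Netherlands". The sample size section bases its 85 cases per condition on a rise in predictive value from 22% to 42%.

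**The concern.** In a randomised trial, conditional adjustment mostly affects precision. Here the method was already in place in some regions, so differences between families can bias the comparison itself. A baseline p-value is a poor guide to that bias. It reflects sample size and the size of the imbalance, but not how strongly the variable is related to the outcome. A modest imbalance in a strong confounder can fail the test and still matter.

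Two features make the rule weaker. Its trigger mentions the children, while education, employment, country of birth and length of residence describe the parents. And the sentence on predictive values, which drive the sample size, does not carry the adjustment language used for the first primary outcome and for parents' needs. PPV rises with the prevalence of true problems even when professionals perform identically, so regional case-mix could be mistaken for part of a method effect.

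**Working it through.** **1. The plan's own figure.** Inputs from the sample size section: 22% versus 42%, power 80%, alpha .05 (taken as two-sided). With mean proportion 0.32,

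n = [1.96·√(2·0.32·0.68) + 0.842·√(0.22·0.78 + 0.42·0.58)]² / 0.20² = (1.293 + 0.542)² / 0.04 ≈ 84.2, rounded up to 85.

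The stated 85 is reproduced. It is the size for a raw comparison of two PPVs, with no covariates.

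**2. What the baseline tests would detect.** The plan tests participants, expected to be 1,750 per condition. The imbalances below are assumed. Power = Φ[(|p1 − p2| − 1.96·SE0)/SE1], with SE0 pooled and SE1 unpooled.

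- 30% vs 33%: SE0 ≈ SE1 ≈ 0.0157; (0.030 − 0.0308)/0.0157 ≈ −0.05; power about 48%.
- 30% vs 35%: (0.050 − 0.0310)/0.0158 ≈ 1.20; power about 88%.
- 30% vs 45%: power above 99.9%.
- 10% vs 12%: about 47%; 10% vs 15%: about 99%.

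Large imbalances would therefore trigger adjustment. Gaps of two or three points would be missed about half the time.

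**3. How PPV moves with prevalence.** Assumed inputs: 10% of children identified and PPV 22% (sample size section), and prevalence 6% (the parent-reported rate at age 1 in the Background). These come from different studies and ages, so joining them is an illustration only.

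- True positives: 0.10 × 0.22 = 0.022. Sensitivity = 0.022/0.06 = 36.7%.
- False positives: 0.10 − 0.022 = 0.078. Specificity = 1 − 0.078/0.94 = 91.7%.
- PPV = sens·p / [sens·p + (1 − spec)(1 − p)].

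Holding sensitivity and specificity the same in both conditions:

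| Prevalence in the other regions (assumed) | PPV | Shift from 22% | Chance that a raw test at 85 per condition shows a difference |
|---|---|---|---|
| 7% | 25.0% | 3 points | about 7% |
| 9% | 30.4% | 8 points | about 24% |
| 12% | 37.6% | 16 points | about 61% |

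The target difference is 20 points. Starting from 10% prevalence instead of 6%, ratios of 1.5 and 2 give PPVs of 30.9% and 38.8%, so the pattern does not depend on the base chosen.

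**4. Room for covariates.** Expected reference-positive cases at 85 per condition: 85 × 0.22 + 85 × 0.42 = 18.7 + 35.7 ≈ 54.

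**The case against.** The strongest reply is that the rule would do little harm. A reader might infer that it misses large imbalances, because at 85 per condition a 30% versus 45% gap reaches significance only about 52% of the time. The document does not support that inference. It describes baseline tests in participants, not among the 85 cases, and at 1,750 per condition that gap is almost certain to be found.

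Three points of wording also count for the plan. The regressions for the share identified and for parents' needs are stated without repeating the condition, and ordinal regression for disclosure can carry covariates. The phrase about the children is probably loose, since the sentence before it speaks of participants and the article uses background characteristics for parental variables elsewhere. The general rule stands ahead of all outcomes, so it could be read to reach the predictive values.

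A reader might also infer that case-mix will produce 8 to 16 of the 20 target points. That needs a 1.5- to 2-fold prevalence difference, for which the document gives no evidence; it describes the regions as comparable overall.

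These replies limit the size of the problem. They do not remove the conditional rule, and if the rule does cover the predictive values, those become subject to the same condition. The comparability statement is made for regions and omits parental education. It cannot stand in for adjustment among the families who consent (70% expected) or become cases.

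**Conclusion.** The point stands in a limited form. A non-randomised comparison should not make its general adjustment rule depend on whether baseline tests show a difference, and the trigger as worded omits the mainly parental confounders. The predictive-value analysis, on which the 85 cases rest, has no adjustment attached to it.

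The demonstrable weakness of the rule lies in modest imbalances, with about 48% power for 30% versus 33%. The effect of prevalence on PPV is arithmetic, but its size here is unknown: about 3 points if prevalence is 7% against 6%, and 8 or 16 points only under the larger assumed ratios. It has not been shown that the regions differ in prevalence, or that all outcomes would go unadjusted. The issue is one of method, and it goes beyond detail left out of a condensed article, because the rule is stated.

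**What to change.** Replace the test-then-adjust rule. Adjust the between-condition comparisons for a short, fixed set already collected, whatever the baseline p-values: child sex, and parental age, education, employment and country of birth. Keep the baseline table descriptive.

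For PPV, fit a logistic regression of reference-positive status on condition plus this set among children identified by the professionals. Interpret it beside the 18-month sensitivity and specificity, which are already planned for all participating children and depend less on prevalence.

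No new data are needed, but the change has a cost. About 54 events will support only a few covariate terms, so education, employment and country of birth should be entered with few categories, and precision may fall slightly. The model also conditions on being identified, which the method is meant to change. Adjustment removes prevalence dependence only so far as the covariates explain the prevalence difference. Residual confounding and prevalence dependence should be acknowledged in the report.

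### The between-condition tests and the 85-case sample size treat children as independent although condition follows region and shared CHPs rate the outcome, so p-values and the stated 80% power are too favourable for any positive intracluster correlation

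*Protocol article*

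**What the plan says.** The Design section compares regions that already use the method with regions that do not. It rules out individual randomization because of contamination, given that "professionals provide care to all children in the region in which they work". Delivery in the intervention regions is by "nurses and medical doctors (N = 57" in all), and the control section reads "The care as usual provided by CHPs (N = 49"). Under Measurements, these same CHPs classify each child at every routine visit, and that classification supplies the first primary outcome.

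The Statistical analyses section compares the identification proportion "using chi-squared tests and logistic regression analysis to correct for potential differences between regions". Met and unmet needs are compared by independent t-tests and multivariate regression, and willingness to disclose by ordinal regression. Predictive values are to be assessed and kappas compared, with no test named for either.

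The sample size section starts from an earlier study of children identified by preventive child healthcare, "of these 22-23% were confirmed by clinical scores on the CBCL filled in by parents". It takes a 20-point increase as relevant, "resulting in an identification rate of 42"%, and concludes "With a power of 80% and a .05 alpha" that 85 cases "in both regions of the country will be needed to detect a change in predictive value of 20"%. It mentions no ICC and no design effect.

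**The concern.** The identification outcome is a professional's judgement. CHPs differ in how readily they flag a child, and CHPs in one team share meetings and, in the intervention regions, intervision groups. Ratings from the same CHP or team are therefore likely to be correlated. The same applies to parents' answers about how free they feel to raise worries with those professionals.

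Because every child in a region has the same condition, variation between CHPs, teams and regions falls entirely into the between-condition contrast. A test that assumes independent children counts that variation as information about the method. Its standard error is too small, and ordinary differences in local practice can be reported as an effect of the family-centered approach. The same omission makes the sample size look sufficient when any clustering reduces its power.

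The wording about differences between regions does not repair this. In context it means covariate adjustment for background characteristics. Region fixed effects could not serve either, since region determines condition and the two would be aliased.

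**Working it through.** **Inputs from the article:** predictive values 22% and 42%; alpha 0.05 (sidedness not stated; two-sided taken); power 80%; 85 cases and 1,750 families per condition; 57 and 49 CHPs. **Assumed, because the article gives neither:** the ICC, and the number of teams or regions per condition.

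**1. Reproducing the plan's figure.** Pooled-variance formula with mean proportion 0.32:

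n = [1.960 × √(2 × 0.32 × 0.68) + 0.842 × √(0.22 × 0.78 + 0.42 × 0.58)]² / 0.20² = (1.293 + 0.542)² / 0.04 = 84.2, so 85 per condition.

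Power at 85 is 80.4%. The formula for independent observations gives the stated figure, so the design effect in it is 1.

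**2. Identification proportion.** If each child is assigned to one CHP, there are 1,750/57 = 30.7 and 1,750/49 = 35.7 children per CHP. Design effect DE = 1 + (m − 1) × ICC. True error of a nominal 5% test = 2 × [1 − Φ(1.96/√DE)].

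| Assumed ICC | DE, intervention and control | True error |
|---|---|---|
| 0.01 | 1.30 and 1.35 | about 9% |
| 0.02 | 1.59 and 1.69 | 12-13% |
| 0.05 | 2.49 and 2.74 | 21-24% |

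For example, at ICC 0.05, 1.96/√2.49 = 1.24 gives 21% and 1.96/√2.74 = 1.18 gives 24%.

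**3. Predictive value, clustering by CHP.** Cases per CHP are 85/57 = 1.5 and 85/49 = 1.7. Power is recomputed at effective n = 85/DE.

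| Assumed ICC | DE | Power |
|---|---|---|
| 0.01 | 1.005 and 1.007 | 80.1% |
| 0.05 | 1.025 and 1.037 | 79.1% |
| 0.10 | 1.049 and 1.073 | 77.9% |

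These assume equal caseloads. With a coefficient of variation of 1 in cases per CHP, power is 76.0% at ICC 0.05.

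**4. Predictive value, clustering by team or region.**

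| Assumed clusters per condition | ICC | DE | Power at 85 | Cases needed |
|---|---|---|---|---|
| 10 (8.5 cases each) | 0.01 | 1.075 | 77.4% | 92 |
| 10 | 0.05 | 1.375 | 66.8% | 117 |
| 5 (17 cases each) | 0.01 | 1.16 | 74.2% | 99 |
| 5 | 0.05 | 1.80 | 55.0% | 153 |

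For example, 1 + (8.5 − 1) × 0.05 = 1.375 and 85/1.375 = 61.8 effective cases. No small-cluster correction is applied, so the rows with few clusters are, if anything, optimistic.

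**5. Margin in recruitment.** The article's interview chain ends at 121 × 0.7 = 84.7 complete cases per condition (175 × 0.7 × 0.7 = 85.75 without rounding), which leaves no margin for a design effect in that subsample.

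**The case against.** Several objections limit the point, and most of them stand in part.

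- **Scope.** A reader might infer that every analysis in the plan assumes independence. The article does not support that. For predictive values and kappas it names no test, so only the sample-size figure and the intervals to be reported are affected there.
- **Cluster size.** The 31-36 children per CHP assume one CHP per child. The Procedure section lists eight visits, and CHPs are both nurses and doctors, so several may rate one child. The 21-24% error is therefore not a property of the plan. It follows from an assumed ICC and a nesting that the article does not state.
- **Power.** A reader might take 67% as the trial's real power. That rests on an assumed 10 teams and ICC 0.05. On CHP-level clustering alone the loss is small, because there are fewer than two cases per CHP.
- **Margin.** The CBCL goes to all participating parents at 18 months, not only to interviewed cases. If 70% of the 175 expected cases returned it (an assumption; about 122 per condition), power would be 92% under independence, about 90-91% with CHP clustering at ICC 0.05, and 77% with 10 teams at ICC 0.05. This does not help the ASQ-SE comparison, which is confined to the subsample.
- **Design section.** Its stated reason against individual randomization is contamination. It does not say that ratings are correlated; that is an inference from the structure it describes.

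An unseen analysis plan does not answer the point, because the article itself fixes the tests and states a sample size.

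**Conclusion.** The point holds for the identification proportion, the parent-reported secondary outcomes and the sample-size figure. The direction is certain for any positive ICC: p-values too small and stated power too high. The size is not known, since the article gives neither an ICC nor a count of teams or regions.

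The likely main damage is to the comparisons that use about 1,750 children per condition, where even an ICC of 0.01 would nearly double the nominal error if each child had one CHP. The loss of power for the predictive value ranges from negligible with CHP-level clustering to material with a small number of teams or regions.

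**What to change.** **Statistical analyses section.** Analyse all between-condition comparisons with a model that carries the PCH team or centre as the cluster: either GEE with small-sample-corrected robust standard errors, or a random-intercept logistic, linear or ordinal model. Add CHP only as a cross-classified effect, or after assigning each child to a main CHP by a stated rule, because a simple CHP intercept is undefined when several CHPs rate one child. Give cluster-based intervals for predictive values and kappas. State the number of teams and regions, and say that inference is limited if regions are few, since neither GEE nor a random intercept is then reliable.

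**Sample size section.** Restate the power of 85 cases per condition over a range of ICCs and the actual number of teams.

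**Cost.** Revised wording and a team identifier (with a CHP identifier if used) kept for each child. Recruitment, visits and questionnaires do not change. Intervals widen and the stated power falls.
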